### Wait-list control group

To ensure fairness in educational opportunity, the control wait-list group will participate in the same educational program as the intervention group after collection of the follow-up data from the intervention group.

### Data collection

After registration of the eligible participants, we will collect individual data at baseline, immediately after the intervention. At baseline, all participants will fill in a web-based questionnaire including demographic information, such as age, gender, education level, position, population size of their municipality, number of residents per PHN in their municipality, their affiliation, previous experience in developing or participating in program development, existence of colleagues or bosses who actively work on program development, and daily practices that will help to build their skills in program planning. We will send the news letters for all participants to prevent drop out. This research was not harmful intervention, so we do not have data monitoring committee.

### Outcomes and assessments

#### Competencies of program planning

The primary outcome, which is competency in program planning, will be measured using the Competency Measurement of Creativity for PHNs (CMC) (Shiomi et al., 2010). The CMC includes 16 self-reported items. The first 3 items measure the competency of PHNs in identifying the necessity of new health services. The next 9 items evaluate skills in the promotion and realization of a service plan. The last 4 items evaluate skills in collaborating with others towards developing a health service. Items are scored on a six-point Likert scale, as follows: 0, not applicable; 1, 20% applicable; 2, 40% applicable; 3, 60% applicable; 4, 80% applicable; and 5, 100% applicable.

#### Knowledge and performance regarding health service development

We will evaluate the educational program using 26 questions regarding the knowledge and practice of PHNs on health service development, at baseline and after the intervention. The participant will fill the questionnaires from 0 (very poor) to 10 (very good) points.

#### Validity and reliability

The scale used to measure primary outcomes used in this study has been confirmed for its reliability and validity, and have been utilized widely in Japan. To ensure data quality, we will collect all data through the original web-site for this study. Additionally, to prevent drop-out from the study, we will send e-mails to all participants and remind them to fill out the web-based follow-up questionnaire.

#### Statistical analysis

Intention-to treat analysis will be utilized to assess the main effect of our intervention. We will calculate the initial drop-out rate as 30%, which will affect the sample size. Even if this rate exceeds 30%, we will not perform an additional recruitment of participants. We will compare the baseline characteristics of the intervention and control group using the *t*-test, and chi-square/Fisher exact test. In addition, ANOVA will be performed to identify factors affecting CMC, and knowledge and behavior regarding program development. To confirm significant improvements in competency, logistic regression analysis will be conducted. PHNs will also be analyzed in groups by years of experiences as PHNs, to identify the group that will benefit the most from participating in our educational program.

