**Methods:**

In this randomized control trial, eligible participants in Japan will be randomly allocated to an intervention group and a control wait-list group. We will provide 8 modules of web-based learning for public health nurses from July to October 2018. To ensure fairness of educational opportunity, the wait-list group will participate in the same program as the intervention group after collection of follow-up data of the intervention group. The primary outcomes will be evaluated using the scale of competency measurement of creativity for public health nurses at baseline, immediately after the intervention. Secondary outcomes will be knowledge and performance regarding program development of public health nurses.

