## Methods

### Study design and settings

This will be a single-blind and parallel group randomized controlled trial. PHNs will be randomized to either the intervention group or the control group [1:1]. After completing the intervention and collecting the follow-up data, the wait-list control group will have an opportunity to participate in the same educational program as the intervention group.

This study will consist of web-based learning modules and face-to-face group sessions. The study participants will take web-based learning modules at their time and place of choice within Japan. After that, PHNs who want to discuss with other participants about community health needs and how to solve it by developing a new health services will join a face-to-face group session that will be held in Sendai and Kobe, Japan.

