### Sample size

We calculated that for an effect size of 0.50, 134 PHNs must be analyzed for the evaluation (intervention group: *n* = 67; control group: *n* = 67). This number is assuming a statistical power of 80% and an alpha value of 0.05 by using G*Power 3.1.9.2. [29, 30] We anticipated a drop-out rate of 30%, and hence concluded that 200 participants will be required.

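### Baseline CMC is collected, but no named outcome analysis states that the arm comparison is adjusted for it; ANCOVA would add precision at no cost in data

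*Protocol article*

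**What the plan says.** The Abstract gives the timing of the primary outcome: "The primary outcomes will be evaluated using the scale of competency measurement of creativity for public health nurses at baseline, immediately after the intervention". Data collection repeats it for all registered participants: "we will collect individual data at baseline, immediately after the intervention". The section on knowledge and performance places the 26-question score at the same two time points.

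Statistical analysis names these methods:
- t-tests and chi-square or Fisher tests to compare the arms' baseline characteristics;
- for the outcomes, "ANOVA will be performed to identify factors affecting CMC, and knowledge and behavior regarding program development";
- a logistic regression to confirm improvement in competency;
- an analysis by years of experience.

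No model terms are listed, and no baseline CMC covariate is mentioned. Adjustment factors come up only in the randomisation text, which sets aside the size of the community and local government. Allocation is by permuted blocks, to keep the group sizes close.

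Sample size states: "We calculated that for an effect size of 0.50, 134 PHNs must be analyzed for the evaluation", "assuming a statistical power of 80% and an alpha value of 0.05". It then allows for loss: "We anticipated a drop-out rate of 30%, and hence concluded that 200 participants will be required".

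**The concern.** When a self-rated scale is measured before and after, each person's baseline score usually carries information about the later one. A model that includes it compares the arms among people with the same starting score. That removes the part of the outcome variance that baseline explains, and it corrects for any chance difference in starting level. The described design does not control that difference, because permuted blocks balance numbers and not competency. Testing baseline characteristics between arms does not change the treatment estimate either.

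The stake is precision. The Discussion expects high drop-out and limited numbers, and Statistical analysis rules out further recruitment if drop-out exceeds 30%. A gain in precision from data already in hand is worth having in that setting.

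**Working it through.** **Inputs.** Effect size 0.50 (SD = 1), 67 per arm analysed, alpha 0.05, power 80%, drop-out 30% and 200 enrolled, all from Sample size. Two assumptions are needed because the article is silent: alpha is two-sided, and r, the correlation of baseline with post-intervention CMC, is taken as 0.3, 0.5 or 0.7. Baseline and post-intervention SDs are taken as equal.

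**Step 1: the plan's own figure.** A two-sample t-test with d = 0.50 needs 64 per arm (128 in total; power 80.1%). A Wilcoxon-Mann-Whitney test with a normal parent has relative efficiency 3/π = 0.955. Since 67 × 0.955 = 64.0, it needs 67 per arm, or 134 in total (power 80.1%), which is the stated number. For drop-out, 134 / 0.70 = 191.4, so 192, which 200 rounds up. The figure therefore matches an unadjusted two-group comparison and appears to take no credit for baseline CMC.

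**Step 2: power at 67 per arm.** Power comes from the noncentral t distribution with noncentrality d × √(n/2).
- Post score only: d = 0.50, noncentrality 0.50 × √33.5 = 2.894, power 81.9%.
- Change score: the variance is multiplied by 2(1 − r), so d becomes 0.50 / √(2(1 − r)).
- ANCOVA: the variance is multiplied by 1 − r², so d becomes 0.50 / √(1 − r²).

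| r | Post score: power | Change score: d | Change score: power | ANCOVA: variance factor | ANCOVA: d | ANCOVA: power |
|---|---|---|---|---|---|---|
| 0.3 | 81.9% | 0.423 | 68.0% | 0.91 | 0.524 | 85.3% |
| 0.5 | 81.9% | 0.500 | 81.9% | 0.75 | 0.577 | 91.3% |
| 0.7 | 81.9% | 0.645 | 96.0% | 0.51 | 0.700 | 98.0% |

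ANCOVA has the highest power in every row. The change score falls below the post score when r is under 0.5.

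**Step 3: chance imbalance.** With 67 per arm the between-arm difference in mean baseline has SD √(2/67) = 0.173 (in SD units). The probability that it exceeds 0.2 SD in either direction is about 25%. A 0.2 SD imbalance shifts:
- the post-score contrast by 0.2 × r = 0.06, 0.10 and 0.14 SD;
- the change-score contrast by 0.2 × (r − 1) = −0.14, −0.10 and −0.06 SD.

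The target effect is 0.50 SD. Adjusting for baseline removes this component under a linear relation.

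**Step 4: heavier drop-out (illustrative).** If only 50 per arm were analysed, post-score power would be 70%. ANCOVA would have 74%, 82% and 93% at the three values of r.

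**The case against.** The strongest objection is that this reads a decision into silence. A condensed article commonly leaves covariate lists to a fuller document, and the section names families of method without model terms. It never says that the comparison is unadjusted. That stands as a limit: a reader might infer that the plan has chosen not to adjust, and the text does not support this. What remains is that the article does name its outcome analyses and none is stated to use the baseline score as a covariate, while a better method is available with data already collected.

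A reader might also infer that baseline scores are used only in the table of baseline tests. That goes too far. Improvement in the logistic model most naturally means change from baseline, and the ANOVA could be group-by-time. Neither use is adjustment, however. As the working shows, a change score has less power than ANCOVA at each r and carries the imbalance in the opposite direction.

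Two further objections limit the size. The 82% figure is for a post-score t-test, which is an assumed reading of the ANOVA; the article names the t-test only for baseline characteristics. And if the analysis is a change score with r = 0.7, the gain is only 2 points (96% to 98%). Both are correct.

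Finally, the trial is not short of power on its own terms. If 30% drop out, 200 × 0.70 = 140 are analysed (70 per arm), and the unadjusted comparison has about 84% power.

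**Conclusion.** The point holds as a free improvement. The named outcome analyses do not state adjustment for baseline CMC, and stating it would give at least as much precision as either plausible reading of the ANOVA.

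At 67 per arm the gain over a post-score comparison is about 3, 9 and 16 percentage points of power for r of 0.3, 0.5 and 0.7. Over a change score it is about 17, 9 and 2 points. The size depends on r, which the article does not give, and on two-sided testing, so the direction is firm and the amount is not.

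Two stronger conclusions should not be drawn. The unadjusted comparison is not invalid or biased: under randomisation its type I error is sound, and the cost is efficiency and robustness. Nor does a chance baseline difference pass in full into a post-score estimate: it is scaled by r, so a 0.2 SD imbalance moves the contrast by about 0.06 to 0.14 SD.

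**What to change.** In Statistical analysis, state one primary model: post-intervention CMC total regressed on arm and baseline CMC total, with the adjusted mean difference between arms and its 95% CI as the primary result. Use the same form for the 26-question score, with its own baseline value as covariate. If the ANOVA and the logistic regression are kept, describe them as supporting analyses.

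The cost is a sentence or two of wording. Both scores are already scheduled at both time points, so no new data, visits or participants are needed, and the sample size can stay as it is.

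### The trial is sized for a two-group comparison of a score, but the method named to confirm improvement in competency is logistic regression; if that means a yes/no CMC outcome, power at 67 per arm is about 44% to 63%, not 80%

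*Protocol article*

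**What the plan says.** The primary outcome is a multi-item score. Under Competencies of program planning the article says "The primary outcome, which is competency in program planning, will be measured using the Competency Measurement of Creativity for PHNs (CMC"), a scale of 16 self-reported items, and "Items are scored on a six-point Likert scale, as follows: 0, not applicable; 1, 20% applicable", and so on up to 5. That section gives no threshold and no definition of a responder.

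Under Sample size: "We calculated that for an effect size of 0.50, 134 PHNs must be analyzed for the evaluation". Split equally, that is 67 in each arm. On the settings behind it, the section says: "This number is assuming a statistical power of 80% and an alpha value of 0.05 by using G*Power 3.1.9.2". The section names no test, no responder rates and no odds ratio. On recruitment it adds: "We anticipated a drop-out rate of 30%, and hence concluded that 200 participants will be required".

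Under Statistical analysis, four things are said about method:
- Intention-to-treat applies to the main effect. This is a principle, and no test is named with it.
- t-tests and chi-square or Fisher tests compare baseline characteristics.
- ANOVA is used to find factors that affect CMC and the knowledge and behaviour scores.
- "To confirm significant improvements in competency, logistic regression analysis will be conducted".

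The last sentence is the only one that ties a named method to confirming improvement in competency.

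**The concern.** A standardised effect of 0.50 with 67 per arm describes two groups compared on a score. Logistic regression without further qualification normally has a binary dependent variable, and speaking of improvement points the same way: improved or not improved. To run it that way, the CMC score must be cut in two. Cutting discards information that the sizing counted on, and the result then depends on where the cut falls.

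Two things are at stake. A programme with exactly the planned effect could miss its confirming test far more often than the 20% that the article accepts. And because no cut is stated, a threshold could be chosen after the data are seen.

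**Working it through.** **Inputs from the article.** Effect size 0.50 (type not named, read as a standardised mean difference d); 67 per arm; power 80%; alpha 0.05 (sidedness not stated, taken as two-sided); allocation 1:1; drop-out 30%; 200 recruited.

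**Assumptions, not in the article.** CMC scores are normal with equal SD, and the programme shifts them by 0.5 SD. The cut is placed so that the control responder rate lies between 10% and 80%.

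**Step 1: reproduce 134.**
- t-test: power comes from the noncentral t with df = 2n − 2 and noncentrality d√(n/2). Solving for 80% gives n = 63.8, so 64 per arm (128). At n = 67, noncentrality is 0.5 × √33.5 = 2.894 and power is 0.819.
- Wilcoxon-Mann-Whitney, asymptotic relative efficiency 3/π for normal scores: effective n = 67 × 3/π = 63.98 and noncentrality is 0.5 × √(63.98/2) = 2.828. Power is 0.801 at 67 per arm and 0.795 at 66. The smallest adequate size is 67 per arm, that is 134, exactly as stated.
- Drop-out: 134/0.70 = 191.4, so 192. The planned 200 covers this and leaves 200 × 0.70 = 140, or 70 per arm.

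So the sizing is sound for a comparison of scores.

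**Step 2: the same effect analysed as yes/no.** For control responder rate p_C, the cut is c = z(1 − p_C) and the intervention rate is p_T = 1 − Φ(c − 0.5). With p̄ the mean of the two rates:

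power = Φ{ [(p_T − p_C) − 1.96·SE0] / SE1 }, where SE0 = √[2p̄(1 − p̄)/n] and SE1 = √{[p_C(1 − p_C) + p_T(1 − p_T)]/n}.

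Best cut, n = 67: p_C = 0.401, p_T = 0.599, SE0 = 0.0864, SE1 = 0.0847. Power = Φ[(0.1974 − 0.1693)/0.0847] = Φ(0.332) = 0.63.

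| Control vs intervention responders | Power, 67 per arm | Power, 70 per arm | Power, 100 per arm | Per arm for 80% |
|---|---|---|---|---|
| 10% vs 21.7% | 0.46 | 0.48 | 0.62 | 152 |
| 20% vs 36.6% | 0.57 | 0.59 | 0.75 | 115 |
| 30% vs 49% | 0.62 | 0.64 | 0.79 | 103 |
| 40.1% vs 59.9% | 0.63 | 0.65 | 0.80 | 100 |
| 50% vs 69.1% | 0.62 | 0.64 | 0.79 | 102 |
| 70% vs 84.7% | 0.53 | 0.55 | 0.70 | 126 |
| 80% vs 91% | 0.44 | 0.46 | 0.60 | 160 |

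A simulated logistic regression on a pooled-median split at 67 per arm gave 0.59, in line with the formula.

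No cut reaches 80% at 67 or 70 per arm. With no drop-out at all (100 per arm), only the most favourable cut does. Reaching 80% would take 200 to 320 analysed, that is 200/0.70 = 286 to 320/0.70 = 458 recruited.

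**Step 3: logistic forms that keep the score.** At 67 per arm, a logistic model with the score as predictor of group gave power 0.83 in simulation. A rank test, used as a stand-in for proportional-odds logistic regression, gave 0.81. The loss comes from cutting the score, not from logistic regression as such.

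**The case against.** A reader might infer that the article plans to dichotomise the CMC, so that 80% power is simply not delivered. The text does not go that far. It names no dependent variable and no cut, and Step 3 shows that a logistic model which keeps the score loses almost nothing. That part of the objection stands: dichotomisation is the ordinary reading, not a written commitment, and the power loss must be stated as conditional on it.

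Nor does the article label logistic regression the primary test. Intention-to-treat is invoked for the main effect without a test, and ANOVA on CMC is a score-scale analysis. If the main test is on the score, power is 80% to 82%. This too stands as a condition. It does not remove the point, because the stated role of ANOVA is to find influencing factors, and only the logistic sentence is about confirming improvement.

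It may be said that the dependent variable and cut belong in an analysis plan that is not shown. Their absence is not the complaint. The article states a sample size and states a confirming method, and under the ordinary meaning of that method the two do not fit. A later plan that keeps binary logistic regression inherits the loss; one that uses a score comparison instead departs from this sentence.

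A reader might also take 134 instead of 128 for an error. It is not: 134 is an exact Wilcoxon-Mann-Whitney size and slightly more than a t-test needs. It costs no power.

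Finally, the power figures rest on assumed normality and assumed responder rates, and they leave out any baseline covariate. They are a range, not a single answer.

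**Conclusion.** The concern holds in conditional form. The 134 belongs to a score comparison at d = 0.50, and the method named to confirm improvement is not tied to it. If CMC improvement is analysed as yes/no and that regression is the main test, then with normal scores and a 0.5 SD shift power at 67 per arm is about 63% at best and about 44% to 46% at the extreme cuts tried. The chance of missing the planned effect would then be about 37% to 56%, against the 20% accepted. If the score stays on its scale, the stated power is essentially met.

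**What to change.** In Statistical analysis, make the confirming analysis the between-arm comparison of the CMC score, kept continuous and reported with a 95% CI. Preferably adjust it for baseline CMC, which is already collected. Move logistic regression to a supportive responder analysis with the cut fixed before the data are seen. In Sample size, name the test to which 134 refers.

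If binary logistic regression is to remain the main test, define the responder and restate its power as dependent on the cut (about 44% to 63% under the assumptions above), not as 80%.

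The cost of the preferred change is a few sentences in the two sections, with no extra participants or data.

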### Study objectives and hypotheses

The aim of this study was to evaluate the following: (1) the effectiveness of the newly designed educational program for developing health service-planning skills of PHNs; and (2) identifying the PHNs that will benefit the most from participating in our educational program. In this report we show our research protocol and an overview of our educational program.

The PICO hypothesis of this study is as follows: (1) participants: middle-level PHNs who have worked in public administration; (2) intervention: providing an educational program regarding development of health services; (3) comparison: providing no program, and (4) outcome: improving the participants’ knowledge and performance of health service planning.

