### Participants

PHNs must meet the following inclusion criteria: (1) have worked on a full-time basis in public administration, and (2) have experience as a municipal or prefectural PHN of ≥5 years and ≤ 20 years [27]. The exclusion criterion is holding a position above the level of unit chief.

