## Discussion

This randomized controlled trial was carefully designed, and aimed to examine the effects of an educational program on improvement of the knowledge and competency of middle-level PHNs regarding health service planning to fulfil community health needs. The strengths of our education program are: (1) developing a user-friendly educational program that combined web-based modules and face-to-face group sessions, (2) participants will be recruited nationwide using clear criteria and will be representative of PHNs in Japan, (3) the program ensures fairness of educational opportunity to participants in the control group, who will have a chance to take the same educational program as the intervention group, and (4) primary outcome measures, including the competency of PHNs, are validated and evaluated using a standardized scale.

We first developed an educational program for middle-level PHNs comprising a combination of web-based modules and face-to-face group sessions. Previous studies only used web-delivered educational modules [32], educational workshops [12], or face-to-face group sessions with homework [13, 15]. Web-based learning methods can overcome time-location restrictions, and will contribute to the nationwide recruitment of subjects, resulting in a sample that is representative of Japan. If our results show a positive effect, our program is expected to contribute to the development of program planning skills of middle-level PHNs, which will be a key to improving health care systems for fulfilling community health needs.

Second, we will provide the same educational opportunity to the control group, which will contribute to identify the effectiveness of our educational program. Assuring equal chance will contribute to prevent the drop-out of participants in the control group, and to accurately understand the effects of the intervention. From the results, we will be able to determine the group of middle-level PHNs that will benefit the most from the program, and the type of skills that can be developed through the program. Using validated and standardized scales will clearly show the effects of the intervention.

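### The second aim, finding who benefits most, names no comparison of the intervention effect between experience groups and is not powered, yet the article says the best group will be determined

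*Protocol article*

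**What the plan says.** Four places in the protocol article bear on this.

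- **Study objectives and hypotheses.** The second of two aims is "identifying the PHNs that will benefit the most from participating in our educational program".
- **Statistical analysis.** The sentence tied to that aim is "PHNs will also be analyzed in groups by years of experiences as PHNs, to identify the group that will benefit the most". The same section states that "ANOVA will be performed to identify factors affecting CMC, and knowledge and behavior regarding program development". It names no arm-by-experience term, number of groups or cut-points.
- **Sample size.** "We calculated that for an effect size of 0.50, 134 PHNs must be analyzed for the evaluation", "assuming a statistical power of 80% and an alpha value of 0.05". This concerns the overall two-arm comparison; nothing is sized for the second aim.
- **Discussion.** "From the results, we will be able to determine the group of middle-level PHNs that will benefit the most from the program".

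Eligibility limits experience to 5 to 20 years: participants must "have experience as a municipal or prefectural PHN of ≥5 years and ≤ 20 years". Nothing in the article labels the second aim exploratory.

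**The concern.** To say that one group benefits most is to say that the intervention-minus-control difference is larger there than elsewhere. That needs a comparison of differences between groups. The ANOVA sentence does not clearly supply one: a factor that predicts the competency score is not thereby a factor that changes the effect of the program.

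If results are instead read group by group, a winner can be named in two ways: by which groups reach significance, or by which has the largest estimate. Both can name a winner when the benefit is the same for everyone. One of the two declared aims could then be answered by chance, and the article announces the answer as something the trial will settle.

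**Working it through.** **Inputs from the article.** Effect size 0.50, 134 analysed (67 per arm), power 80%, alpha 0.05, allocation 1:1, 30% drop-out, 200 recruited.

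**Assumptions, because the article does not give them.** Two-sided tests; two, three or four experience groups of equal size, balanced by arm; the same true effect of 0.50 SD in every group; baseline-outcome correlation r of 0.5 to 0.7 where adjustment is considered.

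**1. The article's own figure.** A two-sided t-test at d = 0.50 needs 64 per arm for 80% power; 67 per arm gives 81.9%. A Wilcoxon-Mann-Whitney test with a normal parent (relative efficiency 3/π) needs exactly 67 per arm, so 134 is reproduced. Allowing for 30% drop-out, 134/0.70 = 191.4, so 192; the stated 200 leaves 200 × 0.70 = 140. The sizing is adequate for the overall effect.

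**2. Reading groups by significance when benefit is equal.** With G groups there are n = 67/G per arm in each. Let p be the noncentral-t power at d = 0.50. The chance that some but not all groups are significant is 1 − p^G − (1 − p)^G.

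| Groups | n per arm per group | Power p | Discordant |
|---|---|---|---|
| 2 | 33.5 | 0.522 | 1 − 0.522² − 0.478² = 0.50 |
| 3 | 22.3 | 0.372 | 1 − 0.372³ − 0.628³ = 0.70 |
| 4 | 16.75 | 0.289 | 1 − 0.289⁴ − 0.711⁴ = 0.74 |

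A simulation of 200,000 trials with whole-number group sizes gave 50%, 70% and 74%. With 140 analysed, the figures are 50%, 71% and 75%.

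**3. Reading groups by the size of the estimate.** Ranking always produces a top group. In the same simulation, with a true effect of 0.50 SD everywhere, the largest minus the smallest estimate averaged 0.27, 0.51 and 0.71 SD for two, three and four groups. The top estimate averaged 0.64, 0.76 and 0.85 SD.

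**4. Effect of baseline adjustment.** Adjustment multiplies the residual SD by √(1 − r²), so d becomes 0.50/0.866 = 0.577 at r = 0.5 and 0.50/0.714 = 0.700 at r = 0.7. Two-group discordance becomes 46% and 31%. Three-group discordance becomes 75% and 70%.

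**5. The comparison that does answer the question.** For two halves, the standard error of the difference between two arm effects is √(4/33.5) = 0.346 SD. Normal-approximation power at two-sided 5%:

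| True difference in benefit | Power |
|---|---|
| 0.25 SD | 11% |
| 0.50 SD | 30% |
| 0.75 SD | 58% |
| 1.0 SD | 83% |

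The difference detectable with 80% power is (1.96 + 0.84) × 0.346 ≈ 0.97 SD. Detecting 0.50 SD with 80% power needs 16 × (2.80/0.50)² ≈ 503 analysed. With adjustment at r = 0.5 to 0.7, the standard error falls to 0.299 to 0.247, and power for 0.50 SD rises to 39% to 53%. When benefit is equal, the interaction test rejects in 5% of trials.

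**The case against.** The strongest reply is that this is a condensed article. Subgroup model form, cut-points and interaction terms often sit in a full protocol or SAP, and neither is shown. A reader might infer from the Statistical analysis section that each group will be tested separately, that p-values will be compared across groups, and that no interaction is planned. The text does not say that. It says only that nurses will be analysed in groups, and the ANOVA sentence neither promises nor excludes an arm-by-experience term. It would also be too strong to say that analysis in groups cannot show a difference in benefit, since group estimates with confidence intervals can be compared properly. This part of the reply stands.

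The figures are also conditional: they depend on an assumed number of equal groups and, for the discordance rates, on reading by significance. Baseline adjustment lowers the two-group rate, but three-group discordance stays at 70% or more.

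The reply does not remove the mismatch. The article itself states the aim, the grouping meant to answer it and the definite conclusion expected, while sizing the trial only for the overall effect. An interaction specified elsewhere would correct the inference, but at this size it would not support a promise to determine the best group.

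A further inference, that future training would be directed to the wrong group, goes beyond the text. No section sets a rule for offering the program by experience.

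**Conclusion.** The point holds in this form: a declared aim has no named comparison of effects, no sample size behind it and no exploratory label, while the Discussion promises a definite answer. With 134 analysed and equal benefit of 0.50 SD, group-by-group reading by significance gives discordant results in about 50% (two groups) to 70% (three groups) of trials unadjusted. For two groups this is about 46% to 31% with assumed correlations of 0.5 to 0.7. Even the right test has about 30% power for a 0.50 SD difference between halves, or 39% to 53% with adjustment. That group-by-group reading is intended is plausible but not stated; that the Discussion overclaims does not depend on it. The primary comparison is unaffected, so this should be changed but does not threaten the main result.

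**What to change.** - **Statistical analysis:** base the second aim on an arm-by-years-of-experience interaction in a model of the CMC score, adjusted for the baseline CMC already collected. Enter years as continuous or in groups fixed in advance, report the difference in effect with a 95% CI, and label the analysis exploratory.
- **Data collection:** record years of experience as a number. Eligibility establishes only that it lies between 5 and 20, and the listed baseline items do not name it.
- **Discussion:** replace the promise to determine the best group with a statement that the trial will explore whether benefit differs by years of experience.

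**Cost:** one questionnaire item if not already planned, one model term and two wording changes, with no extra participants. The article states no baseline-adjusted CMC model, so that model must be written down too. The claim becomes more modest, and power stays low. A linear term could miss a mid-career peak, so effect estimates by prespecified group can be shown descriptively alongside it.
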